# 3. STUDY DESIGN AND METHODS

**3.1 Study design**

The study design is that of a randomised intervention study. Children with confirmed *P. falciparum* malaria, meeting all study inclusion criteria, will be enrolled in the study for a period of 28 days. Participants will be assigned at random to either the intervention or the control group.

The intervention group will receive treatment for malaria plus 1 bag of RUTF per day for 14 days. The control group will receive treatment for malaria without provision of RUTF.

Random allocation to either intervention or control group is thought to be acceptable by the population as RUTF is seen as a medicine rather than a food item. A similar study did not meet a problem with randomisation.[[18]](#footnote-2) For other illnesses, the participants will be offered medical treatment according to the best local standards.

Follow-up visits will be scheduled for directly observed treatment for malaria (day 0, 1 and 2), malaria parasite density and clearance (D0, D2, and until slide is negative; and for weight measurements at day 0, 1, 13 and 27. Weight will be measured twice at each visit by two independent observers. A detailed questionnaire will be conducted at the start, and at day 13 and 27.

All participants who attend follow up sessions at the clinic will receive a small incentive[[19]](#footnote-3)* in order to compensate for lost time due to participation in the study (RUTF will not be given to the control group at the end of the study).

The study will be conducted in the period (May-June) that is likely to have a stable prevalence of malnutrition, a stable incidence of *P. falciparum* malaria and other morbidities (e.g. pneumonia and diarrhoea). The total duration of the data collection will be 2 months for data gathering: 4 weeks of enrolment (40 participants per week) and 4 weeks of follow up (the last follow-up being done 4 weeks after the last enrolment).

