# 4. CASE DEFINITION AND MAIN OUTCOME MEASURES

**4.1 Diagnosis**:

Malaria caused by *P. falciparum* will be diagnosed using a step- wise approach:

1. Screening for clinical signs of malaria
2. Rapid test (Paracheck®)
3. Laboratory confirmation.

During the initial screening of children presenting at the clinic, those with fever >38 degrees and/or a history of fever within the past 2 days will have a rapid test (Paracheck®) performed.[[25]](#endnote-22) Other symptoms that might be related to a malaria infection (e.g. anaemia, splenomegaly, headache) can indicate a Paracheck® to confirm malaria. Cases with a negative Paracheck® will be excluded. In order to exclude false positive Paracheck® test results (the test may remain positive for up to 6 weeks), a positive Paracheck® will be followed by laboratory confirmation (thick blood film). Those with no parasitaemia will be excluded.

In children with a positive blood film for *P. falciparum,* clinical signs will be assessed to exclude severe (complicated) malaria. If anaemia is clinically suspected the haemoglobin will be measured to exclude severe anaemia. Those children with a positive Paracheck®, positive blood film for *P. falciparum* and no other exclusion criteria will be eligible for the study and their caregivers will be asked for consent to enrol.

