# 5. CONFOUNDING FACTORS

There are many factors potentially influencing weight gain or loss other than a given supplement. These confounders may influence the study outcome. In reviewing previous literature, the following known confounders for convalescence15 or for the relationship between malaria and nutritional status6, 9, [[26]](#endnote-23) will be measured:

- Duration of the complaints before attending the clinic [[27]](#endnote-24)
- Duration of symptoms of malaria before attending the clinic
- Age of child (effect modifier 23); as age may be unreliable length/height can be used as a matched variable
- Breastfeeding (partial, as exclusive breastfed children are excluded)
- Disease history (e.g., respiratory tract infections, diarrhoea, vomiting, anorexia) during the last 2 weeks before enrolment
- Incident diseases during the study period
- Socio-economic status of the family
- Educational status of the caretaker and head of the household
- Maternal age
- Nutritional status at baseline
- Being resident or displaced.

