**7.5 Laboratory examination and quality control**

Extra training will be given to the laboratory staff about the rationale and methods of the study. MSF standard procedures for laboratory quality control will be applied. Routinely a thick blood film will be taken at D0 (after the result of the paracheck**®** test is positive) D2 and D13.

Blood films will be examined to determine the presence and the density of falciparum parasites. Slide results will be recorded in ‘number of parasites per microlitre (#/µL)’ and further be rated :+ =1-10 parasites per 100 thick film fields

++ =11-100 parasites per 100 thick film fields

+++ =1-10 parasites per single thick film field

++++ = more than 10 parasites per single thick film field

During the first 3 days of the study 20% of blood slides will be reread by a second microscopist. All weak positive slides will be crosschecked. Discrepant results will be assessed and clarified amongst the two available microscopists. All blood slides will be appropriately stored for future external QC; normal MSF quality control procedures will be implemented: 10% of the slides will be referred to a reference lab (PathCare in Nairobi) for cross-checking. This sample of 10% should show 100% agreement. If not, then all slides will be crosschecked.

Haemoglobin levels will only be assessed when anaemia is clinically suspected, as is the current clinical procedure.

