|  |  |  | | |  | | |  |  | |  | | | |  |
| 7. Has your child had diarrhoea in the last 2 weeks? | | | | | | | | Yes |  | |  | | | |  |
| *(Explain the definition of diarrhoea: at least 3 or more liquid stools per day )* | | | | | | | | No |  | |  | | | |  |
|  |  |  | | |  | | | Don’t know |  | |  | | | |  |
|  |  |  | | |  | | |  |  | |  | | | |  |
| 8. In the last 2 weeks, has your child vomited everything? | | | | | | | | Yes |  | |  | | | |  |
| (persistent vomiting several times) | | | | |  | | | No |  | |  | | | |  |
|  |  |  | | |  | | | Don’t know |  | |  | | | |  |
|  |  |  | | |  | | |  |  | |  | | | |  |
| 9. Do you currently breast-feed your child? | | | | | | | | Yes |  | |  Q 10 | | | |  |
|  | | | | | | | | No |  | |  Q 11 | | | |  |
|  | | | | | | | |  |  | |  | | | |  |
|  | | | | | | | |  |  | |  | | | |  |
| 10. How many times during the day did you breastfeed yesterday? | | | | | | | | …… times | | | | | |  |  |
|  | | | | | | | |  | | | | | |  |  |
| 11. **Since your child was ill**, did she/he eat (food or breast milk) | | | | | | | | Much less | | | | | |  |  |
| less then usual, about the same amount, or more than usual? | | | | | | | | Somewhat less | | | | | |  |  |
| IF LESS, PROBE: Was he/she eating much less than usual or somewhat less? | | | | | | | | About the same | | | | | |  |  |
|  | | | | | | | |  | | | | | |  |  |
|  | | | | | | | | Somewhat more | | | | | |  |  |
|  | | | | | | | | Much more | | | | | |  |  |
|  | | | | | | | | Don’t know | | | | | |  |  |
|  | | | | | | | |  |  | | |  | | |  |
|  |  |  | | |  | | |  |  | | |  | | |  |
| **Part 2: The following questions concern yourself or the entire family** | | | | | | | |  |  | | |  | | |  |
|  | | | | | | | |  |  | | |  | | |  |
|  | | | | | | | | Mother | | | |  | | |  |
| 12: What is your relation to the child? | | | | | | | | Father | | | |  | | |  |
|  | | | | | | | | Grandparent | | | |  | | |  |
|  | | | | | | | | Brother /sister | | | |  | | |  |
|  | | | | | | | | Other | | | |  | | |  |
| 13. What is your own age? (years) …………..years | | | | | | | |  | | | |  | | |  |
|  | | | | | | | |  | | | |  | | |  |
| 14. Where (in what village) do you currently live? ………………………………………….. | | | | | | | |  | | | |  | | |  |
|  | | | | | | | |  |  | | |  | | |  |
| 15.How long have you lived in Dubie or surroundings of Dubie? | | | | | | | | Always | |  | |  Q 17 | | |  |
|  | | | | | | | | …… …. | |  | | Years | | |  |
|  | | | | | | | |  |  | |  | | | |  |

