| 28. Did you get any food aid the last month? | | | | | | | | Yes |  | | |  | | |  |
|  |  |  | | |  | | | No |  | | |  | | |  |
|  |  |  | | |  | | | Don’t know |  | | |  | | |  |
|  |  |  | | |  | | |  |  | | |  | | |  |
| 29. How many meals did the family have yesterday | | | | | | | |  |  | | | meals | | |  |
|  |  |  | | |  | | |  |  | | |  | | |  |
|  |  |  | | |  | | |  |  | | |  | | |  |

| Annex 4 : RUTF for malaria recovery study |
| --- |
| **First and second follow up questionnaire (14 and 28 days)** |

| Study ID |  | | | |  | |  | | |  | | |
| --- | --- | --- | --- | --- | --- | --- | --- | --- | --- | --- | --- | --- |
| Sex | M | | F | |  | |  | | |  | | |
| Date (dd/mm/yy): |  | | | |  | |  |  | |  | | |
|  | | | | | | |  |  | |  | | |
| 1. Did the complaints of your child disappear in the last 2 weeks? | | | | | | |  |  | |  | | |
| If not, why do you think they didn’t? | | | | | | |  |  | |  | | |
|  | | | | | | |  |  | |  | | |
| 2. Has your child been ill with a **fever** at any time in the last 2 weeks? | | | | | | | Yes |  | |  | | |
|  | |  | |  | |  | No |  | |  | | |
|  | |  | |  | |  | Don’t know |  | |  | | |
|  | |  | |  | |  |  |  | |  | | |
| 3. Has your child had an illness with **cough** at any time in the last 2 weeks? | | | | | | | Yes |  | |  Q 4 | | |
|  | |  | |  | |  | No |  | |  Q 6 | | |
|  | |  | |  | |  | Don’t know |  | |  Q 6 | | |
|  | |  | |  | |  |  |  | |  | | |
| 4. When your child had an illness with a cough, did she/he breathe faster than | | | | | | | Yes |  | |  Q 5 | | |
| usual with short, rapid breaths or have difficulty breathing? | | | | | | | No |  | |  Q 6 | | |
|  | |  | |  | |  | Don’t know |  | |  Q 6 | | |
|  | |  | |  | |  |  |  | |  | | |
| 5. Was the fast or difficult breathing due to a problem in the chest or | | | | | | | Chest only | | |  | | |
| to a blocked or runny nose? | | | | | | | Nose only | | |  | | |
|  | |  | |  | |  | Both | | |  | | |
|  | |  | |  | |  | Don’t know | | |  | | |
|  | |  | |  | |  | Other; specify | | |  | | |
|  | |  | |  | |  |  |  | |  | | |
| 6. Has your child had **diarrhoea** in the last 2 weeks | | | | | | | Yes |  | |  | | |
| *(Explain the definition of diarrhoea: at least 3 or more liquid stools per day )* | | | | | | | No |  | |  | | |
|  | |  | |  | |  | Don’t know |  | |  | | |
|  | |  | |  | |  |  |  | |  | | |
| 7. In the last 2 weeks, has your child vomited everything? | | | | | | | Yes |  | |  | | |

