| (persistent vomiting several times) | | | | | |  | No |  | |  | | |
|  | |  | |  | |  | Don’t know |  | |  | | |
|  | |  | |  | |  |  |  | |  | | |
| 8. Has your child visited a health facility since your previous visit? | | | | | | | Yes | |  | | |  |
|  | | | | | | | No | |  | | |  |
| 9. Which medication has your child taken since your previous visit? | | | | | | |  | |  | | |  |
| (other than the anti-malaria) | | | | | | | None | |  | | |  |
|  | | | | | | | Drug: | | | | |  |
|  | | | | | | |  | | | | |  |
| 10. Do you feel the child is completely recovered from the malaria episode? | | | | | | | Yes | | | | |  |
|  | | | | | | | No | | | | |  |
| If not, why do you think the child did not recover yet? | | | | | | | Don’t know | | | | |  |
|  | | | | | | |  | | | | |  |
|  | | | | | | |  | | | | |  |
|  | | | | | | |  | | | | |  |
| 11. **During the last 2 weeks** did she/he eat (food or breast milk)? | | | | | | | Much less | | | | |  |
| less then usual, about the same amount, or more than usual. | | | | | | | Somewhat less | | | | |  |
| *IF LESS, PROBE: Was he/she eating much less than usual or somewhat less* | | | | | | | About the same | | | | |  |
|  | | | | | | | More | | | | |  |
|  | | | | | | | Somewhat more | | | | |  |
|  | | | | | | | Much more | | | | |  |
|  | | | | | | | Don’t know | | | | |  |
|  | | | | | | |  | | | | |  |
|  | | | | | | |  | | | | |  |
|  | | | | | | |  | | | | |  |
|  | | | | | | |  | | | | |  |
| **ATTENTION: Question 12, 13 and 14 are only for the RUTF group on day 13** | | | | | | |  | | | | |  |
|  | | | | | | |  | | | | |  |
| 12. During the last 2 weeks how many days did your child eat 1 complete | | | | | | | ........ days | | | |  | |
| Plumpynut? | | | | | | |  | | | | |  |
|  | | | | | | |  | | | | |  |
| 13. How many plumpynut has your child eaten the last 14 days? | | | | | | |  | | | | |  |
|  | | | | | | |  | | | | |  |
| 14 How many empty sachets are returned? | | | | | | |  | | | | |  |
|  | | | | | | |  | | | | |  |

Thank you.

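### The fever question on the first follow-up form (Annex 4, question 2) reaches back into the enrolling malaria episode, so it cannot identify new fever during the study

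*Protocol*

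**What the plan says.** Section 5 of the protocol lists factors that will be measured because they may influence weight change. It separates two kinds of illness: disease history "during the last 2 weeks before enrolment" and "Incident diseases during the study period". The contribution of other factors to weight change is a specific objective in section 2 and a secondary outcome in section 4.2.

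The form for both follow-up visits is Annex 4. Question 2 (fever) and question 3 (cough) ask about illness "at any time in the last 2 weeks". Questions 4 and 5 follow from question 3. Question 6 (diarrhoea) and question 7 (vomiting everything) use the same two-week recall. Question 8 is anchored differently: "Has your child visited a health facility since your previous visit". Question 9, on medication, uses the same anchor as question 8 and sets the antimalarial treatment aside.

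On timing, section 3.1 states: "A detailed questionnaire will be conducted at the start, and at day 13 and 27". Sections 3.2.4, 6.2 and 6.3 and the heading of Annex 4 say day 14 and day 28.

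On entry, section 4.1 sends for the rapid test "those with fever >38 degrees and/or a history of fever within the past 2 days". It also allows other symptoms to prompt the test.

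**The concern.** Annex 4 question 2 repeats the fever wording of intake question 3 in Annex 3, and Annex 5 gives both the same survey source. At intake, a two-week recall measures illness before enrolment, as intended. Two weeks later the same words cover the period that begins at about enrolment. The answer is yes or no with no onset date, so a yes may mean the enrolling malaria, a new fever, or both.

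At stake is the interpretation of one of the factors that the protocol sets out to study. If nearly all children answer yes, the fever item has little variation to relate to weight gain, and what variation it has mostly reflects who was febrile at enrolment. The same item means something different at the second visit, so the two visits cannot be compared on it.

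**Working it through.** **Step 1: where the recall window opens.** Window start = visit day - 14.

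| Visit | Source of the visit day | Window opens |
|---|---|---|
| First, day 13 | Section 3.1 | 13 - 14 = day -1 |
| First, day 14 | Sections 3.2.4 and 6.2, Annex 4 heading | 14 - 14 = day 0 |
| Second, day 27 | Section 3.1 | 27 - 14 = day 13 |
| Second, day 28 | Sections 3.2.4 and 6.3, Annex 4 heading | 28 - 14 = day 14 |

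Under either timing the first form overlaps the enrolling episode. The second form does not.

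**Step 2: what the overlap does to the answers.** Let q be the share of children who already had the symptom at enrolment, inside the window, and p the share who truly develop it anew. The protocol gives neither, so both are assumptions, and they are taken as independent. Then:

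- share answering yes: P = p + (1 - p)q
- share of yes answers that are truly new: p / P
- correlation of the answer with true new illness: p(1 - P) / √[p(1 - p)P(1 - P)]

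For fever, q is taken as 0.80 to 1.00. It is not fixed at 1 because section 4.1 has a non-fever route to testing, and because a fever that ended before day 0 would fall outside a window opening on day 0. For cough and diarrhoea, which are not entry criteria, q is taken as 0.10 to 0.40. For all items, p is 0.10 to 0.30.

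| Item | q | p | Answering yes | Truly new among yes | Correlation |
|---|---|---|---|---|---|
| Fever | 0.80 | 0.10 | 82% | 12% | 0.16 |
| Fever | 0.80 | 0.30 | 86% | 35% | 0.26 |
| Fever | 0.90 | 0.20 | 92% | 22% | 0.15 |
| Fever | 1.00 | 0.10 | 100% | 10% | none (no variation) |
| Fever | 1.00 | 0.30 | 100% | 30% | none (no variation) |
| Cough or diarrhoea | 0.10 | 0.10 | 19% | 53% | 0.69 |
| Cough or diarrhoea | 0.10 | 0.30 | 37% | 81% | 0.85 |
| Cough or diarrhoea | 0.40 | 0.10 | 46% | 22% | 0.36 |
| Cough or diarrhoea | 0.40 | 0.30 | 58% | 52% | 0.56 |

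In the middle fever row, with 200 children, 0.92 × 200 = 184 answer yes and 16 answer no. Of the 184, 0.20 × 200 = 40 had a new fever and 144 had only the enrolling one.

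**Step 3: the vomiting item.** Annex 2, part A, excludes children who are vomiting everything at enrolment. Question 7 asks about that same sign, so it is less exposed than cough or diarrhoea.

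**Step 4: after re-anchoring.** The enrolment part drops out and P falls to p. For fever, under the same assumptions, the share answering yes goes from 82-100% to 10-30%.

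**Step 5: the section 5 list against Annex 3.** Section 5 lists maternal age and the education of both the caretaker and the head of the household. Annex 3 question 13 asks the respondent "What is your own age", and question 17 asks for the respondent's own schooling. Question 12 allows the respondent to be the mother, father, grandparent, sibling or someone else. Maternal age is therefore recorded only when the mother answers, and the head's schooling only when the head answers.

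**The case against.** The strongest objection is that Annex 4 is not the only planned source. Section 6.2 lists intercurrent illnesses at day 14 and new illnesses under medical history, and section 6.3 does the same at day 28. This stands in part. However, no item in Annex 4, the follow-up form supplied, asks about new illness or its onset, and an examination on the day sees only what is present then.

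A second objection is that the intake form allows a cross-check. Annex 3 records fever, cough, diarrhoea and vomiting in the two weeks before enrolment, so a child without cough at intake and with cough at day 13 can be counted as a new case. This stands for cough and diarrhoea. It does not help for fever, because most children are positive at intake.

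A reader might go further and infer that the whole incident-illness factor will be positive for nearly every child. The protocol does not support that: near-universal positivity follows only for fever, or for a composite that includes fever, and the protocol defines no composite. Nor does question 11, on how much the child ate, share the problem. It is not an incident-illness item, and intake over those two weeks matches the period of the weight outcome.

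A reader might also see a conflict over the follow-up blood film. Section 7.5 takes films routinely at D0 (once the rapid "test is positive) D2 and D13", while section 3.1 speaks of films until the slide is negative, which can coexist with a routine day 13 film. The activity schedule is a collapsed table whose entries cannot be placed by day, and the data analysis section plans no comparison of parasitaemia. No finding can rest on this.

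**Conclusion.** The point holds for the fever item on the first follow-up form. The overlap with the enrolling episode is a matter of day arithmetic and needs no assumption. Its size does: with 80% to 100% febrile inside the window and 10% to 30% with a new fever, 82% to 100% would answer yes, and the correlation with true new fever would be at most 0.26. Cough and diarrhoea are contaminated to a lesser degree (19% to 58% yes under the assumed values) and can largely be rescued from the intake form. Vomiting is less exposed, and the second form is not affected.

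It might be inferred that this weakens the trial's main result. It does not: the primary comparison rests on randomisation and measured weights, and neither depends on this question. What suffers is a secondary objective on contributing factors. This is a minor improvement, but it has to be made before data collection, because no later analysis can split an undated yes. The gap on maternal age and the head's schooling is smaller still, since it concerns only some respondents.

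**What to change.** In Annex 4, questions 2 to 7, replace the two-week recall with new illness since the previous scheduled visit, in line with questions 8 and 9. For the first form, name the starting point as the last directly observed treatment day (day 2 in section 3.1). Saying *scheduled* keeps an unplanned visit from shifting the reference. On the second form the period stays at two weeks (27 - 13 = 14 days). Leave question 11 as it is.

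In Annex 3, add the mother's age and the household head's schooling, or remove these two factors from section 5.

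The cost is a few words on an existing form and at most two short questions, which can go through the questionnaire pre-test already planned in section 8. The downsides are a small departure from the source survey wording, and that an illness beginning during the treatment days themselves would not be counted as new.

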**Annex 5: Sources and justification of questions in questionnaires:**

References:

- Measure DHS Model Questionnaire; With Commentary. Basic Documentation. Number 2 ORC Macro, Calverton, Maryland’ July 2006[[30]](#endnote-27)

-World health survey, B – Individual Questionnaire Rotation – A, World Health Organization, Evidence and Information for Policy. 2002[[31]](#endnote-28)

Pre intake checklist (Annex 2):

A=annex; Q=question. B1: Sick child age 2 months up to 5 years WHO/EMRO chartbook[[32]](#endnote-29)

# Intake questionnaire upon enrolment (Annex 3):

A=annex; Q=question

A3Q2: “You have brought your child because he/she is ill. How many days ago did this episode of illness started?” Adapted from DHS Section 5 Q544: “How many days after the illness began did you first seek advice or treatment?”

A3Q3: DHS Section 5 Q533

A3Q4: DHS Section 5 Q534

A3Q5: DHS Section 5 Q535

A3Q6: DHS Section 5 Q536

A3Q7: DHS Section 5 Q518; case definition diarrhea; Source: Clinical Guidelines, MSF 2007

A3Q8: WHO ind Q6556

A3Q9: new question, in DHS breastfeeding is related to breastfeeding history from birth, therefore in the DHS there is no question about breastfeeding at the day of interview.

A3Q10. Adapted from DHS Congo-Brazzaville: “Hier, combien de fois avez-vous allaité pendant les heures de la journée?” The cut of point we will use for breastfeeding of importance is 2 times per day.

A3Q11: “Yesterday does she/he eat (food or breast milk) less then usual, about the same amount, or more than usual.” IF LES, PROBE: Was he/she eating much less than usual or somewhat less. Adapted from DHS Section 5 521. : “When (NAME) had diarrhea, was he/she given less than usual to eat, about the same amount, more than usual or nothing at all”. The DHS is measuring feeding behaviour during illness, while we want to know whether the child has eaten normally. Breastfeeding considered as food. The answer category of more is removed as it is not distinguishing between somewhat more and much more

A3Q17: WHO Q1009, answer categories are adapted to context

A3Q18 : WHO Q1008

A3Q19: DHS 604

A3Q20: DHS section 8 Q806, added answer categories

A3Q21: DHS section 8 Q811, added answer categories

A3Q22: DHS section 8 Q813,

A3Q23: DHS Household questionnaire 123 added definition of household

A3Q24: DHS Household questionnaire 111and 121 combined and adapted to local context

A3Q25: DHS Household questionnaire 124

A3Q26: DHS Household questionnaire 115, adapted to local context

A3Q27: DHS Household questionnaire 119, adapted to local context

A3Q28: indicator suggested by field team

A3Q29: Indicator used in nutritional surveys

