|  | **Any of the questions above yes? Test Hb; HB<5 g/dL?  Do not enrol in the study and offer normal treatment** | | | | | | | | | | |  |
|  |  | | |  | |  | | |  |  | |  |
| **C. Severe malnutrition** | | | | | | | | | | | | |
|  | 1. Bilateral oedema | | | | | | | Yes | | **No** |  | |
|  | 2. MUAC < 11 cm | | | | | | | Yes | | **No** |  | |
|  | 3. Weight-for-Height < -3sd WHO 2005 reference | | | | | | | Yes | | No |  | |
|  |  | | |  | |  | | |  |  | |  |
|  | **Any of the questions above answered with Yes?  Do not enrol in the study and refer for immediate treatment in the TFP** | | | | | | | | | | | |
|  |  | | |  | |  | | |  |  | |  |
| **D. Other criteria - please tick:** | | | | | |  | | |  |  | |  |
|  | 1. Serious concomitant illness | | | | |  | | |  | Y | | N |
|  | 2. History of allergy to anti malarial drugs | | | | | | | |  | Y | | N |
|  | 3. History of allergy to peanuts or milk | | | | | | | | | Y | | N |
|  | 4. Exclusive breastfeeding | | | | | | | | | Y | | N |
|  | 5. Sibling enrolled in this study | | | | | | | | | Y | | N |
|  | 6. Lives further away than 30 min walking distance | | | | | | | |  | Y | | N |
|  | (check name of village) | | | | | | | |  |  | |  |
|  | **Any of the questions above answered with Yes?  Stop** | | | | | | | | | | |  |
|  |  | | |  | |  | | |  |  | |  |
| **E. Consent:** | | | | | | | | |  |  | |  |
| *Explain the study and read out consent form* | | | | | | | | |  |  | |  |
|  | Guardian > 18 and close relative, gives consent | | | | | | | |  | Y | | N |
|  | |  | | | | | | |  |  | |  |
| Included? | Y | | N |  | | | | |  |  | |  |
|  |  | |  |  | | | | |  |  | |  |
| Study ID number |  | |  |  | | | | |  |  | |  |

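### Annex 3 asks whether the respondent, not the child, is breastfeeding, so a breastfed child brought by another relative is recorded as not breastfed; the Annex 5 cut-off of 2 feeds also lacks a clear unit and boundary

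*Protocol*

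**What the plan says.** Section 5 lists among the factors to be measured: "Breastfeeding (partial, as exclusive breastfed children are excluded)". Section 4.2 makes contributing factors for weight change a secondary outcome, and the last specific objective in section 2 covers the same ground. Under Data analysis, section 10 adjusts the regression for confounders known from earlier studies that also prove significant.

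The factor is collected once, by the Annex 3 intake questionnaire. Question 9 reads "9. Do you currently breast-feed your child"; Yes leads to question 10 and No jumps to question 11. Question 10 reads "How many times during the day did you breastfeed yesterday". Question 12, "12: What is your relation to the child", offers mother, father, grandparent, brother or sister, and other. The consent line in Annex 2, part E, is "Guardian > 18 and close relative, gives consent", so the accompanying adult need not be the mother. Question 19 of Annex 3 also has an answer worded for a male or a female respondent.

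Annex 5 describes question 9 as new. It gives the source of question 10 as "Hier, combien de fois avez-vous allaité pendant les heures de la journée", which refers to daytime hours, and adds directly after it: "The cut of point we will use for breastfeeding of importance is 2 times per day".

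**The concern.** The factor of interest belongs to the child: does this child receive breast milk, and how often? Question 9 asks instead about the person being interviewed. For a mother the two coincide. For any other respondent the truthful answer is No whatever the child's status, and the skip then removes the feed count as well. The error runs one way only, from breastfed to not breastfed.

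The cut-off adds a second, smaller problem. It is expressed per day, but it is attached to an item whose source counts daytime feeds. Two analysts could code the same child differently, and both could cite Annex 5.

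At stake is the quality of one named factor that bears on energy intake alongside the supplement. Moving breastfed children into the reference group shrinks the estimated contribution of breastfeeding. It also makes the factor less likely to pass the significance condition for entering the adjusted model.

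**Working it through.** The protocol gives no figure to reproduce. The cut-off of 2 is stated without derivation, and there are no data on feeding frequency or on who brings the child. The check is therefore mainly a reading of the forms.

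**Step 1: follow the form literally.**

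| Child | Respondent | Question 9 | Question 10 | Recorded as |
|---|---|---|---|---|
| Breastfed by mother | Mother | Yes | Count given | Depends on cut-off |
| Breastfed by mother | Father, grandparent, sibling, other | No (truthful) | Skipped | Not breastfed |
| Not breastfed | Anyone | No | Skipped | Not breastfed |

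With a non-mother respondent, the second and third rows give identical answers. Question 12 shows that the respondent was not the mother, but not which row the child belongs to.

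**Step 2: look for another source.** Annex 2, item D4, concerns the child but covers exclusive breastfeeding only, so every enrolled child should be a No. Question 11 of Annex 3 and question 11 of Annex 4 mention breast milk when asking how much the child ate, but do not ask whether the child is breastfed. Annex 4 has no breastfeeding item. Section 6.1 lists exclusive or partial breastfeeding under medical history, but no annexed form has a child-level item for partial breastfeeding.

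**Step 3: unit and boundary of the cut-off.** Take a child fed once by day and three times at night: 1 + 3 = 4 feeds in 24 hours, but question 10 records 1. If the 2 means 24-hour feeds, this child is misclassified. If it means daytime feeds, the child is classified as intended. A child with exactly 2 counted feeds falls on either side, depending on an inclusiveness rule that is not given.

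**Step 4: size, as illustration only.** Every input here is an assumption.

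- *Respondent error.* Let p be the share of children who are breastfed, and q the share of those recorded No because of who answered. If the error is unrelated to weight gain, the unadjusted breastfeeding contrast is multiplied by (1 − p)/(1 − p + pq). With p = 0.5 and q = 0.15 this is 0.5/0.575 = 0.87, a shrinkage of 13%. With q = 0 there is none. Neither value can be checked: eligibility spans 6 to 59 months, and children brought by other relatives may be breastfed less often than those brought by their mothers.
- *Day-only counting, if the 2 means 24-hour feeds.* Assume Poisson feeds with mean m, a fraction f of them by day, and exactly 2 counting as important. The share of children with at least 2 feeds in 24 hours who score below 2 is [P(day < 2) − P(total < 2)]/P(total ≥ 2). For m = 4 and f = 0.5 this is (0.406 − 0.092)/0.908 = 35%. Over m = 3 to 8 and f = 0.5 to 0.7 it runs from 2% to 45%. If the 2 means daytime feeds, it is 0 by definition.
- *Boundary.* If the 2 means daytime feeds, the share of breastfed children with exactly 2 is e^(−mf)(mf)²/2. For mf = 2 (m = 4, f = 0.5) this is 0.135 × 4/2 = 27%. For mf = 5.6 (m = 8, f = 0.7) it is 0.0037 × 31.36/2 = 6%. The missing inclusiveness rule decides how those children are coded.

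**The case against.** A reader might infer that the plan applies a 24-hour threshold to a daytime count and so systematically under-scores breastfed children. The documents do not support that. The cut-off stands in the entry for question 10, directly after the daytime wording, and can be read as a threshold on that daytime count. Under the same Poisson assumptions with means 3, 4, 6 and 8, a 24-hour cut-off of at least 2 would class about 80%, 91%, 98% and 99.7% of breastfed children as important. It would then add little to a yes/no item, which favours the daytime reading. What stands is that Annex 5 does not say which is meant.

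A reader might also infer that asking about yesterday, close to or during the illness, lowers the count. Onset may be the day of the visit, and question 11 allows for eating more as well as less, so the direction is not established.

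On the respondent, it is fair to say that trained interviewers may rephrase question 9 for a father or grandparent, that a pre-test is planned, and that question 12 identifies the records at risk. But the form gives no instruction to rephrase, and identifying a record does not restore the child's status or feed count.

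Finally, the coding of a covariate is often left to a statistical analysis plan. That answers the boundary question, because the raw count is kept. It does not answer question 9: an analysis plan cannot recover what was never asked.

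**Conclusion.** The point holds for the respondent wording, and as a need for clarification of the cut-off. Followed literally, Annex 3 records some breastfed children as not breastfed and loses their feed count, with no other annexed item to correct it. Only children whose respondent is not the breastfeeding mother, and for whom a literal No is recorded, are affected. A child whose mother answers is affected only by the unclear cut-off, and not at all when the daytime count exceeds 2.

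The number affected cannot be derived from the protocol, and the percentages above show only how the result depends on assumptions. The consequence is limited to the secondary outcome on contributing factors and to covariate adjustment. Intake answers are baseline information and allocation is random, so the comparison of RUTF with control is not biased, and no sample-size, power or significance figure changes. This is a minor point, worth making because the correction is nearly free before the forms are used.

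**What to change.** Before the pre-test in section 8:

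1. Reword question 9 to *Is the child currently breastfed?* Annex 5 calls this item new, so no comparability with a source survey is lost.
2. Reword question 10 to *How many times was the child breastfed yesterday …?*, so that it too refers to the child, with a don't-know option for respondents who cannot give a count.
3. State in Annex 5 whether the cut-off of 2 applies to daytime or 24-hour feeds, word question 10 to match, and state whether exactly 2 counts as important.

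The cost is two reworded items and one line in Annex 5. A non-mother may report the count less accurately than a mother would, but the yes/no status will be right. If the 24-hour unit is chosen, question 10 departs from its source item. Asking instead about a usual day before the illness is optional: it trades one recall problem for another and is not needed to resolve this point.
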